**Methods:**

We use a randomized controlled trial with two intervention groups: a live workshop with and without additional reminders. The workshop intervention design consists of a baseline measurement, two workshops, and one follow-up measurement. Each workshop takes place in small groups (*n* < 11). We use a randomized allocation to both groups. To control for health-related effects and the expected behavior change we examine (i) physical activity (i.e. active time, taken steps, etc.) by a tracking device (ii) physical wellbeing, motivation, and volition by an online questionnaire, and (iii) participants also report physical activity by a diary. All measurements are taken one week before the respective workshop and 24 weeks after the initial baseline measures.

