The participation should motivate and offer new perspectives of increasing physical activity at the workplace. We have also designed the workshop in such a way that our concept can be used in various companies. In this first step, we want to prove our concept in medium-sized organizations. Due to the current pandemic situation, there is an increasing number of people working in separate offices without any contact with other co-workers. To ensure that these changes do not lead to increased inactivity, new work-related health offers or activity programs should be established. We developed a workshop which takes all the above-mentioned points into account. The use of computer prompts combined with providing information reduces sitting time on average by 14 to 96 min per day*.* In this early stage, we want to prove the concept of our live approach in small groups and hypothesize that the participants show positive health effects (i.e. well-being, decreased MSD) and positive adaptations in their health behavior (i.e. increased physical activity). We hypothesize that additional reminders improve health-related effects. In addition, we want to develop our workshop design in the framework of eHealth applications or a web-based solution, since the integration of such approaches might improve the efficiency of health programs at work [37].

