## Methods

### Participants

We recruit office desk workers aged between 18 and 67 years from different organizations (i.e. public administration with standard office workplaces) in Germany. Two intervention lines are planned: one live workshop group with and one without reminders. After attending the first workshop participants in the appropriate intervention group will receive reminders via e-mail twice a week. The e-mails remind the participants of the possibilities to be physical active at the work place previously introduced through the workshop. Overall, eight e-mails will be sent until participants answer the second online survey one month after participating in the workshop. We use a randomized allocation of the participants to both groups. As inclusion criteria, we define an age group between 18 and 67 years and the employee council of each institution has to approve the participation. Additionally, participants are asked not to take part in other studies during the time of the workshop intervention. Participants are excluded if they take part in only one workshop or do not fill in the questionnaires (missing answers > 30%) appropriately. All participants will be informed about the content and objectives of our study, they can ask questions, and they can withdraw from the participation at any time. As a prerequisite for participation, participants of our study sign a declaration of consent. A meta-analysis [38] revealed small intervention effects of workplace physical activity interventions (d = 0.21). Based on this assumption, power-analysis (G-Power 3.1) indicated in sum 168 participants for an ANOVA with repeated measures (within-between interaction). Our calculation included *f* = 0.11, *α* = 0.05, β = .80, three groups, and three measurements.

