#### Nordic musculoskeletal questionnaire (NMQ)

This questionnaire aims to detect musculoskeletal stress in different regions of the body [40]. The NMQ consists of two parts: first, general information about the participant including the individual situation at work, and second, detailed questions about previous and existing physical stress. The latter also examines special regions of the body (i.e. neck, shoulder, lower back). All questions include the duration and frequency of physical stress, especially during the last 12 months and the last seven days. Previous research concluded that the NMQ is sensitive, repeatable, and a useful screening tool [41]. We use this questionnaire in two ways: (i) as a screening tool to adapt the physical activities in our refresher-workshop, and (ii) to record changes in physical stress a few weeks after the workshop.

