### Statistics

All data are processed to enhance quality; for example, in case of missing data, we conduct a missing value analysis (MVA) with a subsequent imputation procedure. Outliers are checked manually. Then, it is planned to perform analyses for repeated measurements of physical wellbeing, HAPA subscales, and the results from the physical activity diary. Results from the Nordic Musculoskeletal Questionnaire are analyzed descriptively. For all analyses, the significance level is set to 0.05.

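### Decreased musculoskeletal disorders is a stated hypothesis with no planned between-group inference, and the NMQ's 12-month items would be a poor measure of change

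*Protocol article*

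**What the plan says.** The Introduction of the protocol article states the aims. The authors "hypothesize that the participants show positive health effects (i.e. well-being, decreased MSD", and they add a between-group aim: "We hypothesize that additional reminders improve health-related effects".

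The section on the NMQ gives the instrument two uses. One is screening, to adapt the activities of the refresher workshop. The other is "to record changes in physical stress a few weeks after the workshop". On recall it says: "All questions include the duration and frequency of physical stress, especially during the last 12 months and the last seven days".

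The Statistics section separates the outcomes. For three of them, "it is planned to perform analyses for repeated measurements of physical wellbeing, HAPA subscales, and the results from the physical activity diary". For the fourth: "Results from the Nordic Musculoskeletal Questionnaire are analyzed descriptively".

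Two places fix the timing. The Participants section says reminders run "until participants answer the second online survey one month after participating in the workshop". The abstract says: "All measurements are taken one week before the respective workshop and 24 weeks after the initial baseline measures".

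**The concern.** The two hypothesised health effects stand side by side in the Introduction, but the Statistics section gives a repeated-measures analysis to only one of them. A fall in symptoms seen in a descriptive table cannot be credited to the workshop or to the reminders without a comparison between groups and a statement of its uncertainty. As planned, the trial would report on MSD without being able to support or reject what it hypothesised.

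The choice of NMQ items adds a hazard. The questionnaire has a 12-month and a seven-day recall period, and the article does not say which is meant to show change. Both follow-ups come well inside 12 months of the workshop. Answers to the 12-month items would therefore still largely describe the time before it, and a real improvement could pass for little or no effect.

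**Working it through.** **1. Aim against analysis.**

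| Outcome | Hypothesised effect (Introduction) | Planned analysis (Statistics) |
|---|---|---|
| Well-being | yes | repeated measures |
| MSD, by the NMQ | yes | descriptive |

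The article is not silent on the NMQ. It states a method, and that method does not serve the stated aim.

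**2. The plan's own figure.** The Participants section gives 168 participants for a within-between interaction with f = 0.11, alpha = 0.05, power 0.80 (printed as beta), three groups and three measurements. The correlation between measurements is not stated; 0.5 is assumed here.

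- Noncentrality = f² × N × m / (1 − rho) = 0.0121 × 168 × 3 / 0.5 = 12.2.
- Degrees of freedom: (3 − 1)(3 − 1) = 4 and (168 − 3)(3 − 1) = 330.
- Power = 0.803, so 168 is reproduced. Assumed correlations of 0, 0.3 and 0.7 would give 333, 234 and 102.

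The effect size comes from a meta-analysis of workplace physical activity interventions. The figure is therefore not in dispute, but it says nothing about power for MSD.

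**3. How much of a 12-month window precedes the intervention.** Inputs: a 52-week window; second survey about 4 weeks after the first workshop; first workshop about 1 week after baseline; last survey 24 weeks after baseline, hence about 23 weeks after the workshop. Share before = (52 − w) / 52.

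| Survey | w (weeks) | Share before |
|---|---|---|
| One month, from the workshop | 4 | 48/52 = 92% |
| One month, from baseline | 5 | 47/52 = 90% |
| Last, from the workshop | 23 | 29/52 = 56% |
| Last, from baseline | 24 | 28/52 = 54% |

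The section on study aim and procedure puts the last survey at six months. Read as 26 weeks after baseline, the share would be 26/52 = 50%.

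A seven-day window reaches back only to about 3 weeks after the workshop at the second survey, and to about 22 weeks after it at the last. It does not touch the pre-workshop period at either.

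**4. What this does to a 12-month prevalence (illustration).** The article gives no prevalence or effect, so all inputs here are assumptions: episodes at a constant rate, 12-month prevalence p0, and a rate reduced by a fraction r from baseline on. With L = −ln(1 − p0), the prevalence reported w weeks after baseline is 1 − exp(−L × (1 − r × w/52)).

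- p0 = 50%, r = 50%, w = 4: 1 − exp(−0.693 × 0.962) = 48.6%, a fall of 1.4 points.
- p0 = 50%, r = 50%, w = 24: 1 − exp(−0.693 × 0.769) = 41.3%, a fall of 8.7 points.
- Across p0 of 30-70% and r of 30-100%, the fall is 0.6 to 2.9 points at 4 weeks and 3.5 to 22.3 points at 24 weeks.

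A 12-month yes/no item is thus nearly blind at one month and attenuated at 24 weeks.

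**The case against.** Four arguments weigh against the point.

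*The 12-month items can register change.* A reader might infer that a 12-month item must show no change over follow-ups this short. The arithmetic does not support that. At the last survey some 44-46% of the window falls after the intervention, and the illustration gives falls of up to 22.3 points. The NMQ also asks about duration and frequency, which can drop even in someone who would still answer yes for the past year. The argument that a person with symptoms in the 28 weeks before baseline stays positive at the last survey holds only for a yes/no item. This objection stands, and the wording here is limited accordingly.

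*The article never makes the 12-month items the change measure.* This is true. Seven-day items are listed beside them, and a descriptive analysis of those would fit the text. The recall point is therefore a caution about a choice left open, not an error in a stated choice.

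*A descriptive analysis may still show groups, time points and intervals.* It may. What the Statistics section withholds is a planned inferential comparison, in contrast to the other outcomes.

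*Descriptive handling is reasonable for a proof of concept.* The sample size rests on an activity effect, and the NMQ's first listed use is screening. That would settle the matter if MSD were called exploratory. It is instead named among the hypotheses, so the mismatch remains.

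**Conclusion.** The point holds in a limited form. The MSD hypothesis, and the reminder hypothesis so far as it covers MSD, have no planned between-group inference, because the Statistics section restricts the NMQ to description. This conflict follows from the text alone and rests on no assumption.

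The second part depends on the survey timing and on which items are used. If the 12-month items were taken as the change measure, about 90-92% of their window would precede the intervention at one month and about 54-56% at 24 weeks. That is near-blindness followed by attenuation. The documents do not support the stronger reading that the NMQ as a whole cannot measure change, since its seven-day items can do so at both follow-ups.

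The sample size of 168 and the analyses planned for the other outcomes are unaffected.

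**What to change.** In the Statistics section, name the seven-day NMQ items as the MSD change outcome. Report baseline-adjusted between-group estimates with 95% confidence intervals, labelled as secondary and not separately powered. Two contrasts are needed:

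- **Workshop arms against control, at the post-study questionnaire.** This addresses whether the workshop reduces MSD. Both workshop arms attend the workshop, so comparing them with each other cannot answer it. The control group is described as completing a questionnaire only before and after the study, so no one-month contrast is available.
- **Reminder against no reminder, at both follow-ups.** This addresses the reminder hypothesis.

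The first contrast assumes that the control group's questionnaire includes the NMQ; the plan should confirm this. The article describes random allocation to the two workshop groups and does not say how the control group is formed. The plan should state this, because it decides whether the first contrast is a randomised one.

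Keep the 12-month items for baseline description and for tailoring the refresher workshop.

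Alternatively, if the NMQ stays descriptive, label MSD exploratory or remove its decrease from the hypotheses in the Introduction. Either route resolves the conflict.

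The cost is a few lines of text. The NMQ is already part of the online questionnaire, and the Data Availability statement says the study has not begun. The downside of the first route is one more secondary analysis that 168 participants were not planned for, so its intervals may be wide.

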### Intervention

The first workshop lasts about two hours, the refresher workshop only one hour. Each workshop consists of active and passive parts. Table 1 describes the first workshop including active and passive parts. The refresher workshop includes some new activities (see part III in Table 1) as well as an interactive question-answer part. In the latter participants can ask questions about the workshop and further individual strategies, and can discuss adaptations. This concept is used in a live workshop with and without reminders. The reminders are used to retain the acquired contents and knowledge of the first workshop and to give incentives for physical activity.

**Table 1 Tab1:** Description of main contents during the workshop; participants were actively (i.e. physically active) or passively involved

***Part***	***Content***	***Participants’ involvement***
I	Workshop trainers give some general information about inactive lifestyle and behavior (i.e. statistics) at German workplaces and resulting health-related issues (i.e. physically, social, psychological), based on recent studies. Different concepts for increased physical activities at the workplace are shown and participants are asked in anonymized live-questions about their daily physical activity.	passive
II	The trainers give instructions on adequate health safety standards regarding the office desk setting, based on German laws and regulations. This includes the rights & duties as well as the health-related behavior of office workers at their workplace (i.e. position of the desk, equipment, sitting/standing positions) in Germany. Again, the participants are asked for their participation in anonymized live-questions about these topics.	passive
III	Trainers show some exercises from the areas of mobilization, strengthening, and stretching. All examples can be performed at the workplace. At the end of this tryout, some recommendations for physical activity (i.e. how long and often exercises should be performed) are given.	active
IV	Trainers and participants of the workshop discuss opportunities and barriers to daily physical activity in individual group activities. Experiences are shared and the group works on the conception of action plans. Finally, each participant should create his/her plan.	active

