#### Questionnaire of physical well-being (FEW-16)

The FEW-16 contains some statements about the body, physical capacity, and relaxing. It is a retrospective assessment of the general situation during the last three weeks. Therefore, participants have to indicate the extent to which they agree with the individual statements. The questionnaire contains four scales each includes four items (i.e. stress resistance, ability to enjoy, vitality, and inner peace). Each item is assessed by a six-point Likert scale with a range from zero: “not applicable at all” to five: “fully applicable”. Kolip and Schmidt (1999) reported high internal consistencies (i.e. α = .82 to .92) for the total scale and the subscales and validated the questionnaire with questionnaires on quality of life and functional impairments [42]. Although the FEW-16 contains four scales, in a non-clinical context the physical well-being seems to be one-dimensional [43]. Thus, in our study, we will use the sum-score of all sub-scales. The score ranges from zero to 80 points, in which higher scores represent higher well-being.

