**Fig. 2 Fig2:**
[figure not shown]
HAPA-model by Schwarzer R. (adapted from Schwarzer, 2008)

The questionnaire contains different subscales (i.e. self-efficacy, planning, intention, outcome expectations, and risk perception). Subscale items are assessed by a four-point Likert scale (i.e. from zero = “not applicable at all” to three: “fully applicable”), except the risk perception with a five-point Likert scale. Scores are computed by adding or averaging the answers over all items.

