## Discussion

We introduced a workshop to increase health-seeking behaviors in office workplaces in Germany. Our workshop is based on a combination of physical activity and health behavior planning.

At first, we want to indicate one minor limitation regarding our data acquisition: we have to validate our PAD. The diary is adapted to a validated questionnaire; however, that questionnaire has not been validated for daily usage. Moreover, the literature showed differences between self-reported (i.e. by questionnaires) and accelerometer-measured physical activity [48, 49]. Therefore, we use accelerometer-measured physical activity to prove our PAD in a sub-sample of our participants. If the result of our analysis shows insufficient validity, only the data from the accelerometry will be used. Another limitation refers to the recruitment process. The participants are recruited in different organizations and therefore have different pre-conditions (i.e. workplace equipment, health services) as well as differently effective health counsellors. Thus, we will collect data on the organization to control for potential experimenter effects between organizations.

In addition, there is some risk of inter-subject group bias if individuals in one group inform a member of the other group about reminders. In the follow-up survey, we will ask the group without reminders whether they received information about the procedure in the other group. We can then perform analyses according to whether participants received information about the other group and exclude them from the analyses, where necessary. Participants of the workshops might be less active in winter. Hence, the season could affect the amount of physical activity. As data of both intervention groups will be collected in the same season, they remain comparable. All these issues could affect our results and should be critically reviewed later.

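### No primary endpoint is named and at least seven outcomes are each tested at 0.05: the false positive risk is about 10–14% for the tested outcomes named in the workshop hypothesis, and about 18–30% if HAPA subscales may also count

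*Protocol article*

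**What the plan says.** The protocol's Statistics section plans "analyses for repeated measurements of physical wellbeing, HAPA subscales, and the results from the physical activity diary" and then sets one rule for everything: "For all analyses, the significance level is set to 0.05". The Nordic Musculoskeletal Questionnaire is outside this rule in practice: "Results from the Nordic Musculoskeletal Questionnaire are analyzed descriptively".

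The number of tested outcomes follows from the instrument descriptions:
- **FEW-16:** one score ("in our study, we will use the sum-score of all sub-scales").
- **HAPA:** five subscales ("The questionnaire contains different subscales (i.e. self-efficacy, planning, intention, outcome expectations, and risk perception").
- **Diary:** one sum score weighted by energy cost.

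Accelerometry is not in the Statistics list, but the Discussion lets it take the diary's place: "If the result of our analysis shows insufficient validity, only the data from the accelerometry will be used".

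The Introduction gives two hypotheses. The one on the workshop names well-being, fewer musculoskeletal disorders and more physical activity. The one on reminders names no outcome: "We hypothesize that additional reminders improve health-related effects".

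The Participants section derives 168 participants from f = 0.11, alpha 0.05, power 0.80 (printed as β), three groups and three measurements, for a within-between interaction. It does not say on which outcome. No section ranks the outcomes or mentions an adjustment for multiple tests.

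**The concern.** The sample size assumes one test at 0.05, while the analysis section applies 0.05 to each of at least seven. With no outcome ranked first, a reader of the results cannot tell which test decides whether the workshop or the reminders worked, and the chance that some test is significant by accident exceeds 5%.

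The outcomes also differ in standing. The HAPA constructs are, on the protocol's own account, steps on the way to behaviour, and the Introduction reports studies in which self-efficacy and other social-cognitive factors had only indirect effects on activity, or none. One construct, planning, is taught directly: of the workshop's last part, Table 1 says "Finally, each participant should create his/her plan". A gain in planning with no change in activity or well-being is therefore a realistic result, and the wording of the reminder hypothesis leaves room to report it as a success.

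Two features add to the room for selection. The activity measure may change after a validity check with no stated threshold, and the outcome assessors and data analysts are not blinded (Study-aim and procedure).

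**Working it through.** **1. The plan's own figure.** Inputs from the Participants section: k = 3 groups, m = 3 measurements, f = 0.11, alpha = 0.05, power 0.80. The correlation between repeated measurements is not stated; I assume ρ = 0.5 with sphericity.
- λ = f²·N·m/(1 − ρ) = 0.0121 × 168 × 3/0.5 = 12.20
- df1 = (k − 1)(m − 1) = 4; df2 = (N − k)(m − 1) = 165 × 2 = 330
- Power from the noncentral F distribution = 0.803

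So 168 is reproduced, for a single interaction test at 0.05. Other correlations give 333 (ρ = 0), 234 (0.3) and 102 (0.7).

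**2. Number of tests.** FEW-16 (1) + HAPA (5) + diary (1) = 7. If accelerometry replaces the diary, the count stays at 7; if it is tested as well, it is 8. The Nordic questionnaire adds none.

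**3. Chance of at least one false positive, all null hypotheses true.** For k independent tests it is 1 − 0.95^k. For correlated tests I use 400,000 simulated sets of equally correlated two-sided z-tests. The protocol gives no correlations between outcomes, so 0.3 to 0.7 is an assumed range.

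| Tests counted | Independent | ρ = 0.3 | ρ = 0.5 | ρ = 0.7 |
|---|---|---|---|---|
| 2: well-being, diary | 9.8% | 9.5% | 9.1% | 8.4% |
| 3: plus accelerometry | 14.3% | 13.7% | 12.5% | 10.9% |
| 7: well-being, diary, five HAPA | 30.2% | 27.2% | 23.0% | 17.9% |
| 8: plus accelerometry | 33.7% | 30.1% | 25.1% | 19.0% |

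Under any dependence, the upper bound for seven tests is 7 × 0.05 = 35%.

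**4. What a correction over all seven would cost.** Bonferroni uses 0.05/7 = 0.00714 per test. On the inputs of step 1, power at 168 falls from 0.803 to about 0.55, and 80% power needs about 249 participants. One primary endpoint at 0.05 leaves 168 unchanged.

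**5. Power if reminders against no reminders were primary.** Assume three equal groups, 168/3 = 56 per arm, d = 0.21 and within-person correlation 0.5.
- Change from baseline: variance factor 2(1 − 0.5) = 1, so the expected z is 0.21 × √(56/2) = 1.11. Power = Φ(1.11 − 1.96) plus a negligible opposite tail ≈ 20%.
- Adjusted for baseline: variance factor 1 − 0.5² = 0.75, so the expected z is 1.11/√0.75 = 1.28. Power ≈ 25%.

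**The case against.** The workshop hypothesis is not open-ended. It spells out well-being, musculoskeletal disorders and physical activity, and no HAPA construct is among them. Musculoskeletal disorders are only described, so two tests, or three with accelerometry, bear on it. This stands, and it is why the figure for that hypothesis is about 10–14%.

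A reader might infer that any of the seven outcomes can satisfy the hypotheses. For the workshop hypothesis the text says otherwise. For the reminder hypothesis it is a possible reading: no outcome is named, the study aim is put in the same general terms, and the Abstract lists motivation and volition, the two HAPA stages, among what is examined. The text permits that reading without stating it.

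A reader might also take 30% as a ceiling. It is not: it assumes exactly seven independent tests, positive correlation lowers it, an eighth test raises it, and the bound for seven is 35%. Nor is 1 − 0.95^14 = 51% supported. It needs a separate, independent test at each follow-up, whereas the sample size describes one interaction over all three measurements, and repeated measurements on the same people are correlated.

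Each single test does hold its 5% level; what is missing is control across tests. The study calls itself an early proof of concept, and the method of adjustment may sit in an analysis plan that is not shown. The register entry is also not shown and might rank the outcomes. These points lower the weight of the concern but do not remove it, because this document itself fixes 0.05 for all analyses without ranking any outcome.

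**Conclusion.** The concern holds in a limited form. At least seven outcomes are tested at 0.05 each, none is primary, and 168 is attached to none. The chance of at least one false positive is two to three times nominal (9.8–14.3%, independent tests) for the tested outcomes named in the workshop hypothesis. It reaches about 30% (independent), or about 18–27% (correlations 0.7 to 0.3), only if a HAPA subscale is allowed to count as success. All these figures assume that every null hypothesis is true; the correlations are assumed. The point should be settled before the study starts; it does not invalidate the design.

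**What to change.** Before enrolment (Data Availability says the study has not begun):
- Name one primary endpoint: physical activity, measured by one instrument fixed in advance. Remove the later switch from diary to accelerometer for this endpoint; otherwise the selection problem stays inside it.
- Test it at 0.05 with the group-by-time interaction for which 168 was calculated, and limit the general 0.05 statement to this test.
- Make well-being and the group or reminder contrasts secondary, with a Holm correction.
- Report the HAPA subscales as process measures that cannot by themselves support a claim of effect.

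One condition must be checked. The calculation of 168 uses three groups and three measurements, but Study-aim and procedure gives the control group only questionnaires before and after the study. The same section sends accelerometers to all consenting participants, while the Discussion speaks of a sub-sample for comparing them with the diary. The sponsor should confirm that the chosen instrument is collected in every group and at every occasion in the test. If it is not, 168 does not apply and must be recalculated.

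If the sponsor prefers reminders against no reminders as the primary contrast, the sample size must be redone. Power would be only about 20–25% under the assumptions of step 5, and d = 0.21 is cited for workplace activity interventions, not for the addition of e-mails.

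Cost: wording in the protocol, and in the register entry if that does not already rank the outcomes. With the interaction as primary, 168 need not rise on the plan's own inputs. The downside is that fewer results can be claimed as significant.
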